Does regular meditation practice after initial instruction increase mental well-being?	The amount of meditation practice during approximately the first year predicts practitioners’ mental well-being, such that a greater amount leads to greater mental well-being.	A number of 242 gives 95% power to detect the variance in mental well-being (SWEMWBS^b^) explained by monthly meditation practice observed in linear mixed model analysis, at a 2-tailed significance level of 0.05, accounting for an estimated 20% loss to follow-up.	Linear mixed model of the fixed effect of the amount of meditation in the past month on mental well-being in the past 2 weeks (SWEMWBS), controlling for the confounding factors of age, caring status, education, mental health diagnosis, commitment to meditation, and membership of a practice support community at baseline.	A positive/negative and statistically significant association between the amount of meditation in the past month on mental well-being in the past 2 weeks will suggest that regular meditation practice after initial instruction increases/decreases mental well-being in a linear fashion. A nonsignificant association will suggest an absence of evidence for this.
Is the effect of continued meditation practice after initial instruction on quality of life moderated by whether a practitioner’s meditation tradition is spiritual or secular?	Whether the meditation tradition is secular or spiritual will moderate any effects on quality of life (nondirectional)	Sampling plan follows hypothesis 1, with an additional 20%, n=627, powered to detect effect of f^2^=0.0318	Linear mixed model of the fixed effect of the amount of meditation in the past month and the interaction effect of tradition spirituality on quality of life in the past week (EQ-HWB-9), controlling for the confounding factors of age, caring status, education, mental health diagnosis, commitment to meditation, and membership of a practice support community at baseline.	A positive/negative statistically significant beta coefficient for this interaction will indicate that regular meditation practice within a spiritual tradition will have a larger/smaller effect on quality of life than practicing within a secular tradition. A nonsignificant association will suggest absence of evidence for this.

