### Sampling Plan

#### Hypothesis 1

Sample size calculation for quality of life measured by the EQ-HWB-9 using repeated measures linear mixed modeling assumes three groups will be assessed with (1) low, (2) medium, and (3) high regular meditation dosage. Given the limited research on the effects of long-term regular meditation practice, calculating power is challenging. We have therefore used conservative power calculations that may err on the side of underestimating the power of our primary analysis but allow for use of the effect information and analytic tools that are available. We have conducted power analysis using 3 levels of variation in the predictor of monthly meditation amount, rather than the continuous variable we plan to use in our final analysis. This is to allow for the use of an analytic power calculation method for our repeated measures design, rather than simulation measures, which would be highly speculative with the limited real and independent data available for our outcome measure [64]. Ten measurement time points were also used, rather than the 12 that will be included in our analysis, as this is the maximum for GLIMMPSE (University of Florida and University of Colorado Denver) power analysis software [65].

Sample size calculation for quality of life measured by the EQ-HWB-9 using repeated measures linear mixed modeling assumes three groups will be assessed with (1) low, (2) medium, and (3) high regular meditation dosage. No increase in EQ-HWB-9 scores was predicted for the low meditation group [58]. For the high meditation group, we estimate a stepwise increase to a minimum of a 2.25-point EQ-HWB-9 increase (out of a possible 9‐45 points) from baseline to time point 5, corresponding to the change in EQ-HWB-9 from baseline to 6 months associated with improvement in mental health in a validation of the EQ-HWB-9 sensitivity to change [59]. We then predict a further 2.25-point increase to time point 10, for a total increase of 4.5 points. For the moderate meditation group, stepwise improvement was predicted with a minimum of a 2.25-point EQ-HWB-9 increase from baseline to time point 10. Baseline EQ-HWB-9 is set at 19.6, with an SD of 7.0, as per our nationally representative surveys [66]. Using GLIMMPSE [65] with 95% power and 0.05 2-tailed type 1 error rate, sample size was calculated at 435 participants. We estimated a 20% loss to follow-up over one year, bringing the sample size required to 522 participants.

#### Hypothesis 2

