There is limited research available on the effects of long-term meditation on mental well-being using the 7-item SWEMWBS. However, there is published data available for the 14-item version (Warwick-Edinburgh Mental Well-being Scale; WEMWBS) for postinitial meditation instruction [22] and at one year follow-up [23]. These 2 mental well-being scales are highly correlated (0.954) [61], so we have used the data available for the WEMWBS in our power calculation.

Sample size analysis for the effect of meditation practice amount on mental well-being (WEMWBS) using repeated measures linear mixed modeling assumes three groups will be assessed with (1) low, (2) medium, and (3) high meditation dosages, with 10 measurement time points, as required for the use of GLIMMPSE [65] as an analytic power calculation method outlined above. The baseline mean WEMWBS is set at 49.61, the postintervention level found for the introductory meditation arm, and the SD of 8.88 [22] for all groups and time points. No increase in WEMWBS scores [62] is predicted for the low meditation group. For the moderate meditation group, we predict stepwise improvement of 3 points to a final time point mean of 51.06 (SD 8.88), corresponding to a one-year follow-up of an MBP, regardless of regular meditation rates after course completion [23]. For the high meditation group, we estimate stepwise improvement to an 8-point increase from baseline to final time point (mean 57.61, SD 8.88), representing a minimum individual detectable change that has been reported for the WEMWBS [63]. Using GLIMMPSE [65] with 95% power and 0.05 2-tailed type 1 error rate, the required sample size to detect these effects was 201 participants, 242 assuming a 20% loss to follow-up.

#### Hypotheses 3 and 4

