There is limited research investigating whether meditation practice being spiritual or secular moderates the effect of practice time. Previous studies have shown evidence that engaging in regular spiritual mind-body practices may moderate the effect of an initial meditation program at 6 months, such that stress and depressive symptoms are only improved compared to treatment as usual for those individuals who do not regularly engage in spiritual mind-body practices [67]. However, this was not compared to similar secular meditation practices. Our prospective longitudinal study found that those with a spiritual goal for meditation practice obtained less benefit from their meditation practice for life satisfaction and positive affect [32]. Nevertheless, to our knowledge, the moderating effect of practicing within a spiritual tradition on quality of life or well-being as outcomes is yet to be investigated or observed over a one-year follow-up. Therefore, potential effect sizes for these analyses are highly uncertain. As such, to account for testing these hypotheses, we plan to increase our sample by an additional 20% from what is required for power to test our primary outcome (Hypothesis 1) to 627 participants. With this sample and our planned model, setting power to 0.95 and significance to 0.05 2-tailed, we will be powered to detect a moderation effect of f^2^=0.0352 [68].

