For hypothesis 1, we will perform linear mixed model analysis of the fixed effect of the amount of meditation in the past month on quality of life in the past week (EQ-HWB-9), controlling for the potentially confounding baseline factors of age, caring status, education, mental health diagnosis, commitment to meditation practice, and membership of a meditation practice community at baseline. This model will allow us to assess how meditation as practiced by our participants under naturalistic conditions contributes to their quality of life, controlling for baseline differences related to time available for practice, symptom severity, motivation, and social support. If we detect an effect of meditation practice, we will perform sensitivity analysis to examine how robust this effect is to time-varying confounders by using inverse probability weighting of meditation in the last month to examine if the association would still be present if practice that month had varied independently of prior practice and benefit.

For hypothesis 2, we will perform linear mixed model analysis of the fixed effect of the amount of meditation in the past month on mental well-being in the past 2 weeks (SWEMWBS), controlling for the potentially confounding factors of age, caring status, education, mental health diagnosis, commitment to meditation practice, and active membership of a meditation practice community at baseline. If we detect an effect of meditation practice, we will again perform time-varying confounding sensitivity analysis with inverse probability weighting.

For hypothesis 3, we will add the variable capturing whether participants practiced secular meditation traditions (with no more than one month of reported practice in a spiritual tradition) versus engaging in spiritual traditions and its interaction term with the amount of meditation to the model for hypothesis 1. This initial analysis will allow us to assess whether predominantly secular meditation has a differential effect from meditation that incorporates spiritual practices, as practiced in real-life contexts, while retaining sufficient power. If we detect an effect, we will perform further exploratory analysis into what may be driving this difference. We will also describe the groups in terms of meditation practice characteristics, including proportion of practice types and social context.

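### Hypothesis 3 is called sufficiently powered after a flat 20% increase, but 95% power needs a slope difference of about 1.7 to 1.9 times the average practice slope at an even split, and the two printed detectable effects conflict

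*Protocol article*

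**What the plan says.** Hypothesis 1 is sized in the Sampling Plan for 95% power with three dose groups and ten time points: "sample size was calculated at 435 participants". Attrition is then added: "We estimated a 20% loss to follow-up over one year, bringing the sample size required to 522 participants". For Hypothesis 2, "the required sample size to detect these effects was 201 participants, 242 assuming a 20% loss to follow-up".

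For moderation, the Sampling Plan concedes that effect sizes are very uncertain and then states: "we plan to increase our sample by an additional 20% from what is required for power to test our primary outcome (Hypothesis 1) to 627". With "setting power to 0.95 and significance to 0.05 2-tailed", it gives a detectable moderation effect of f²=0.0352. The Hypothesis 3 row of Table 1 reads "Sampling plan follows hypothesis 1, with an additional 20%, n=627" but gives f²=0.0318. The Hypothesis 4 row gives n=291 and f²=0.045.

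The Analysis Plan tests Hypothesis 3 by adding one binary tradition variable and its product with practice amount to the Hypothesis 1 model. It says this compares the traditions "as practiced in real-life contexts, while retaining sufficient power". That phrase appears only there. The groups are formed at follow-up from the baseline and monthly tradition reports (Measures), and no expected secular:spiritual split is given. The abstract plans a cohort of 600, not 627.

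**The concern.** Hypotheses 3 and 4 are stated hypotheses in Table 1, not exploratory analyses. Testing whether two groups have different slopes is much harder than testing whether the pooled slope is zero, and a 20% larger sample makes up little of the gap. The statement that power is sufficient therefore needs two things the article does not supply: a slope difference worth detecting, and the share of participants in each tradition.

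The printed f² values do not fill the gap. There are two for the same hypothesis and sample size, they are not related to the expected practice effect, and they are set at the enrolled number although the plan expects 20% loss. A reader cannot tell that a moderation as large as the average practice effect could well be missed on the primary outcome.

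**Working it through.** **Inputs.** From the Sampling Plan: two-sided alpha 0.05; power 0.95; n=435 (Hypothesis 1) and n=201 (Hypothesis 2) before attrition; 20% loss; n=627. From Table 1: n=291 for Hypothesis 4. From the abstract: 600. Retained numbers: 627 × 0.8 = 502 and 600 × 0.8 = 480. The split is not stated, so 50:50 (best case) and 80:20 are shown as assumptions.

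**Step 1: the sample sizes reproduce.** 435 × 1.2 = 522, and 522 × 1.2 = 626.4, rounded up to 627. 201 × 1.2 = 241.2, rounded up to 242, and 242 × 1.2 = 290.4, rounded up to 291. After loss, 502/435 = 1.15, so the retained sample is only 15% above what Hypothesis 1 itself needs.

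**Step 2: the printed effect sizes.** I used the noncentral F test with noncentrality f² × n. For one tested term, the noncentrality for 95% power is (1.960 + 1.645)² = 12.99, so f² is about 12.99/n; the exact F values are as follows.

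- One term: 0.0208 at n=627, 0.026 at 502, 0.027 at 480.
- f²=0.0318 at n=627 is reproduced with five tested terms, and 0.0352 with seven.
- f²=0.045 at n=291 is reproduced with one tested term.

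So the two Hypothesis 3 figures rest on different tests. Neither is the single interaction term in the Analysis Plan, whereas the Hypothesis 4 figure is.

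**Step 3: detectable slope difference.** Let p be the share in one tradition, with similar practice variance in both. Then

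Var(slope difference) = Var(overall slope) / [p(1 − p)],

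and p(1 − p) is at most 0.25. Suppose n₁ participants give 95% power for the average slope as a 1-df test. With n participants, the multiple m of the average slope needed for 95% power is

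m = 1 / √[p(1 − p) × n/n₁],

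and power for a difference of m times the average slope is

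Φ(m × √[p(1 − p) × n/n₁] × 3.605 − 1.960).

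Example, Hypothesis 3 at n=627 and 50:50: m = 1/√(0.25 × 627/435) = 1/√0.360 = 1.67. For m=1, power = Φ(0.600 × 3.605 − 1.960) = Φ(0.20) = 58%.

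| Hypothesis, n₁ → n | m, 50:50 | m, 80:20 | Power at m=1, 50:50 | Power at m=1, 80:20 |
|---|---|---|---|---|
| H3, 435 → 627 | 1.67 | 2.08 | 58% | 41% |
| H3, 435 → 502 | 1.86 | 2.33 | 49% | 34% |
| H3, 435 → 480 | 1.90 | 2.38 | 47% | 33% |
| H4, 201 → 627 | 1.13 | 1.42 | 89% | 72% |
| H4, 201 → 502 | 1.27 | 1.58 | 81% | 63% |
| H4, 201 → 480 | 1.29 | 1.62 | 80% | 61% |
| H4, 201 → 291 | 1.66 | 2.08 | 58% | 41% |

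**Step 4: dependence on the Hypothesis 1 test.** The article does not state which contrast, or which correlation, GLIMMPSE used to reach 435. If that test had more degrees of freedom, 435 corresponds to a larger noncentrality and so to a larger slope. The Hypothesis 3 multiple then shrinks by √(12.99/λ):

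- 2 df, λ=15.44: 1.53 at n=627 and 1.75 at 480 (50:50).
- 18 df (group by time), λ=29.62: 1.10 at n=627 and 1.26 at 480 (50:50).

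It stays above 1 in each case.

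**The case against.** Four points count on the other side.

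- **Candour.** The Sampling Plan admits the uncertainty and reports a detectable effect. It does not say that 20% offsets the cost of an interaction, and the power phrase can be read as the reason for using only two groups. Table 1 also says that a nonsignificant interaction shows only a lack of evidence. This stands, and it limits the harm. A reader might infer that a null result would be presented as proof of no moderation; the documents do not support that.
- **Conservative sizing.** The article says its three-group calculation may understate the power of the primary analysis. That is fair, and it makes the multiples conditional (Step 4). It does not bring any of them down to 1.
- **The 95% standard.** At 80% power and 50:50, the multiple is (1.960 + 0.842)/3.605 times the 95% figure: 1.29 at n=627 and 1.45 at 502. The standard is the plan's own, but even at 80% the difference must exceed the average slope under the 1-df assumption.
- **Variance.** Because both printed Hypothesis 3 values exceed the main effect's f² of about 12.99/435 = 0.030, a reader might infer that moderation must explain at least as much variance as the whole meditation effect. That mixes tests. On the one-term basis the detectable interaction is 0.021 to 0.027, below 0.030.

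**Conclusion.** The concern holds for Hypothesis 3. Power is called sufficient without a target difference or a split. At the plan's own 95% standard, the test detects only a slope difference of about 1.7 to 1.9 times the average slope at 50:50, and about 2.1 to 2.4 times at 80:20. This rests on three assumptions: that 435 gives 95% power for a 1-df slope, that practice variance is similar in both groups, and that the split lies in the range shown. With a higher-df Hypothesis 1 test the multiple could be as low as about 1.1 at 50:50; the direction is unchanged.

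A reader might extend the 1.7 to 1.9 range to Hypothesis 4. That is right only for the n=291 in Table 1. The whole cohort of 600 to 627 serves Hypothesis 4, where the multiple is about 1.1 to 1.3 at 50:50.

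The conflict between f²=0.0352 and 0.0318 at the same n, and the mismatch of both with a one-term interaction, rest on none of these assumptions about slopes or splits.

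**What to change.** In the Analysis Plan, remove the phrase on sufficient power. In the Sampling Plan and Table 1, replace 0.0352 and 0.0318 with one detectable effect for the single interaction term at the retained sample (about 0.026 at 502, or 0.027 at 480 if 600 are enrolled). Express it also as a slope difference relative to the Hypothesis 1 slope, over a stated range of secular:spiritual splits, and name the Hypothesis 1 test on which that ratio rests. Describe Hypothesis 3 as powered only for large moderation. Give the detectable effect for Hypothesis 4 at the cohort actually planned, not at n=291.

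The cost is wording and a less favourable account of Hypothesis 3: the f² becomes smaller than either printed value, but the slope multiple shows how large the moderation must be. No extra participants are needed.

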### This Study

This study seeks to investigate the long-term effects of meditation practice on quality of life and well-being in current ecological contexts through longitudinal examination of a cohort of beginner meditators who intend to continue practicing over one year. Specifically, this study aims to estimate the effectiveness of regular meditation practice after initial instruction for promoting quality of life (Aim 1, primary outcome) and mental well-being (Aim 2). We hypothesize that the amount of regular meditation practice during approximately the first year after initial instruction will predict practitioners’ quality of life, such that more regular practice predicts greater quality of life (Hypothesis 1). We also hypothesize that the amount of regular meditation practice during approximately the first year after initial instruction will predict practitioners’ mental well-being, such that more regular meditation will predict greater mental well-being (Hypothesis 2).

The study further aims to test whether the meditation tradition being secular or spiritual moderates any effects on quality of life (Aim 3). We hypothesize that whether participants’ meditation practice is predominantly secular or includes engagement with spiritual practices will moderate any effects on quality of life (Hypothesis 3, nondirectional). We further aim to test whether the meditation practice being secular or spiritual moderates any effects on mental well-being (Aim 4). Mental well-being captures the flourishing spectrum of mental health, and there may be moderation effects detectable in this domain that would not be evident for quality of life [33], either due to a lack of effect or because those relationships are obscured by potential ceiling effects in negatively worded quality of life measures. We hypothesize that whether the meditation tradition is secular or spiritual will moderate any effects on mental well-being (Hypothesis 4, nondirectional).

The study also aims to explore the cost-effectiveness of regular meditation practice on quality of life (Aim 5). Given that this is a cohort study and we will not have a control group as we would in an RCT, we will conduct an exploratory economic analysis using a comparator group of those not continuing with meditation compared to those that are, accounting for confounding factors.

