For hypothesis 4, we will add the secular versus spiritual variable and its interaction term with the amount of meditation to the model for hypothesis 2.

To address aim 5, we will conduct an exploratory cost-effectiveness analysis using participants who did not continue meditating as a comparator to participants with ongoing meditation practice, while accounting for relevant confounding factors. We will use the EQ-HWB-9 to measure outcomes, applying index values from the United Kingdom pilot value set over time to create QALYs [60]. Costs will include those for mental health service use (psychological support) across one year plus costs of meditation practice. To calculate the incremental cost-effectiveness ratio (ICER) from a public health perspective, we will calculate the difference in costs between the low- and high-meditation dosage groups and divide by differences in QALYs. The ICER represents the additional cost of the intervention for each additional unit of health benefit gained. We will investigate the cost-effectiveness of the ICER against thresholds of the 4 included countries, as available, to determine how likely the intervention will be cost-effective from a public health perspective. Issues of confounding will be addressed through statistical adjustments as per the main analysis, and we will conduct relevant scenario analyses. We will conduct deterministic (one-way) sensitivity analysis to estimate the impact of uncertainty around effects by varying output and cost parameters, displayed on tornado graphs. We will conduct probabilistic sensitivity analysis to explore the combined parameter uncertainty over 10,000 iterations, displayed on a cost-effectiveness plane.

To address aim 6, we will estimate the incidence of participants first reporting adverse effects by reporting the proportion and confidence intervals of first adverse experiences that also impaired participants’ daily function. We will also report descriptive statistics of the frequency, severity of impairment of daily function, and duration of impairment of meditation-related challenging experiences and MRAEs.

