The study also aims to conduct an economic evaluation in the form of an exploratory cost-effectiveness analysis to investigate costs and outcome comparisons associated with regular meditation practice. As this study is a cohort study and not an RCT where we would usually see cost-effectiveness analysis conducted, and as there is no control group, we plan to construct an exploratory cost-effectiveness analysis using a comparator group of those not continuing to meditate. This is a major limitation to the cost-effectiveness analysis proposed in this study.

There are further limitations regarding effects and costs. Although the EQ-HWB-9 has been shown to be valid for measuring quality of life in people who meditate [76], there are currently no country-specific value sets for the EQ-HWB-9 for Australia, New Zealand, or the United States. We will have detailed information on costs due to psychological care; however, we will need to estimate costs from this information for the relevant country’s health systems where costs are not out-of-pocket. This analysis is further exploratory on the basis of the direction of the effect. For instance, if, through partaking in meditation practice, participants decide to pursue mental health support, this will increase costs but may also increase outcomes. Hence, lowering mental health support costs may not be the objective here. We acknowledge the potential opportunity cost of meditation practice, and while we will be able to provide information on the time commitment needed to achieve benefit in our primary analysis, we are unable to address this in the current exploratory cost-effectiveness analysis. As the outcomes look at change in QALYs over one year, we will also not be able to take into account changes in effects and costs during this period for the base analysis. We may be able to do further exploratory analysis investigating the associations between costs and effects over time in a future study.

Finally, the study aims to estimate the incidence of MRAEs. We anticipate the incidence of MRAEs will be around 10%, in line with previous research [42]. We also expect the average impact on daily function to be small, on average, but that some participants will experience significant impairment to daily function. We plan to conduct a future mixed methods examination of MRAEs to explore their predictors and phenomenology.

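### The Aim 5 ICER is given two different contrasts, and the adjustment set it borrows leaves out baseline utility and baseline cost

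*Protocol article*

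**What the plan says.** All references are to the Protocol article.

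**Contrast.** The Aim 5 paragraph of the Analysis Plan sets up the evaluation "using participants who did not continue meditating as a comparator to participants with ongoing meditation practice". The section This Study agrees ("using a comparator group of those not continuing with meditation compared to those that are, accounting for confounding factors"), and so does the Discussion ("using a comparator group of those not continuing to meditate"). Later in the same Analysis Plan paragraph the ICER is defined differently: "we will calculate the difference in costs between the low- and high-meditation dosage groups and divide by differences in QALYs". Low, medium and high dose occur elsewhere only in the Sampling Plan, as a simplification for the power software. That section says the real analysis will use practice amount as a continuous variable. The Aim 5 row of Table 1 names no groups.

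**Adjustment.** "Issues of confounding will be addressed through statistical adjustments as per the main analysis". For Hypothesis 1 the listed covariates are age, caring status, education, mental health diagnosis, commitment, and practice community membership. Table 3 schedules EQ-HWB, meditation cost and mental health care cost at baseline, monthly and one year.

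**QALY construction.** The Analysis Plan describes "applying index values from the United Kingdom pilot value set over time to create QALYs". The Discussion, among its limitations, says "we will also not be able to take into account changes in effects and costs during this period for the base analysis".

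**The concern.** An ICER is a ratio of two differences between the same two groups. If the text names two pairs of groups, two analysts can follow it faithfully and report different ratios, and the choice could be made after the results are seen. The ratio will be compared with the thresholds of four countries, so the choice matters even in an exploratory analysis.

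Under either contrast, the groups form by self-selection after baseline. Those who keep meditating, or meditate more, may have started with better or worse utility and with different service use. If baseline index value and baseline cost are left out of the adjustment, part of any such difference can pass into the QALY and cost differences.

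The QALY wording adds a smaller uncertainty: one section can be read as using the whole utility path, the other as setting within-year movement aside.

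**Working it through.** The article states no ICER, QALY difference or cost difference, so there is no figure to reproduce. The steps below show how far each ambiguity could move the effect denominator. Units are EQ-HWB-9 score-point-years, because the article gives no utility values. Changes are treated as gains, as the Sampling Plan treats them.

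**Inputs (Sampling Plan, Hypothesis 1).** Low group: no change. Medium: +2.25 by time point 10. High: +2.25 by time point 5 and +4.5 by time point 10. Baseline SD 7.0.

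**Assumptions not in the article.** Ten time points spread evenly over one year, linear change between the stated points, equal thirds in the dose groups, and a share s of the cohort that stops, all of them within the low third.

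**1. Area for each group**
- High: (0 + 2.25)/2 × 4/9 + (2.25 + 4.5)/2 × 5/9 = 0.500 + 1.875 = 2.375
- Medium: 2.25/2 = 1.125
- Low: 0

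**2. The two contrasts**
- High versus low: 2.375 − 0 = 2.375
- Ongoing versus stopped: (2.375/3 + 1.125/3)/(1 − s) = 1.167/(1 − s)

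| s | Ongoing − stopped | Share of high − low |
|---|---|---|
| 10% | 1.30 | 55% |
| 20% | 1.46 | 61% |
| one third | 1.75 | 74% |

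The cost numerator would also come from different people. No cost figures are given, so its change cannot be sized.

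**3. Baseline gap left unadjusted.** Assume a gap of 0.2 SD = 0.2 × 7.0 = 1.4 points that shrinks linearly to a share r of itself by one year. The area it adds is 1.4 × (1 + r)/2.
- r = 0.5: 1.05, and 1.05/2.375 = 44% of the planned high-versus-low effect
- r = 1: 1.40, and 1.40/2.375 = 59%

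**4. Within-year path.** Compare the full area with a trapezoid using baseline and one year only, which is 4.5/2 = 2.25 for any shape that ends at +4.5.

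| Path | Full area | Two-point | Two-point error |
|---|---|---|---|
| Planning path | 2.375 | 2.25 | 5% too small |
| Plateau by month 3 | 0.25 × 2.25 + 0.75 × 4.5 = 3.94 | 2.25 | 43% too small |
| Gain only after month 9 | 0.25 × 2.25 = 0.56 | 2.25 | four times too large |

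The article does not specify a two-point calculation. This step shows only what is at stake if the Discussion sentence were applied literally.

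**The case against.** The strongest reply is that Aim 5 is exploratory and carries no hypothesis, that the Discussion already calls the constructed comparator a major limitation, and that cut-offs for the groups can be left to a fuller plan. This stands as far as it goes. It lowers the weight of the point, and the missing cut-offs alone would be no finding. But the disclosure concerns the stopped-meditating comparator and does not mention the low/high formula. A fuller plan cannot implement two conflicting contrasts as one base case. The planned one-way and probabilistic analyses vary parameters; they do not settle who is compared.

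On adjustment, the Analysis Plan also promises to account for relevant confounders and to run scenario analyses, and it mentions a longitudinal constrained analysis, which might imply some handling of baseline. The inverse probability weighting for Hypothesis 1 refers to prior benefit. None of this places baseline index value or baseline cost in the Aim 5 adjustment. The constrained analysis is not explained, and the weighting is a conditional sensitivity analysis of monthly practice.

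Three stronger readings are tempting and not supported:
- A reader might infer that low-dose participants are still meditating and that a medium group is dropped from the ICER. The article does not define the Aim 5 groups, so low could include or mean those who stopped, and no medium group need exist.
- A reader might infer that the monthly utilities will be discarded. Only the Discussion sentence points that way. It can also be read as saying that one annual ratio does not describe how costs and effects move during the year.
- A reader might infer that any starting gap is counted in full as QALY gain. The Discussion speaks of change in QALYs, which, if it means change from baseline, would remove a constant gap. That is not specified in the Analysis Plan, and it would over-correct a gap that shrinks: with r = 0.5 above, 1.05 − 1.40 = −0.35.

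**Conclusion.** The point holds in this form. The Analysis Plan gives two contrasts for one ICER, so the ratio is not uniquely defined; that is a plain contradiction in the text. On the planning trajectories the second contrast has 55% to 74% of the effect denominator of the first, given equal thirds and 10% to one third of the cohort stopping, all from the low third.

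The listed adjustment set omits baseline index value and baseline cost, which leaves the ratio open to confounding. The article does not show that it is confounded, and the size is unknown; the 44% to 59% rests on an assumed 0.2 SD gap of which 50% to 100% persists.

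The within-year issue is a secondary inconsistency between two sections and is not what leaves the ICER undefined. Its effect is about 5% on the planning path and much larger in either direction for early or late gains. No primary or secondary hypothesis is affected. The change is worth making because the result will be judged against national thresholds.

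**What to change.** 1. Name one base-case contrast, define it by one practice rule applied to the weekly reports, and use the same groups for costs and QALYs. Report the other contrast as a scenario. Align This Study, the Analysis Plan and the Discussion.
2. Adjust QALYs for baseline index value and costs for baseline cost, in addition to the main-analysis covariates.
3. State that QALYs are the area under the baseline, monthly and 12-month index values and that monthly costs are summed. Reword the Discussion sentence on within-year changes to agree, keeping whatever limitation the authors intended, for example that a single annual ratio does not model how costs and effects move together over time.

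The cost is wording and minor programming. All the data are already scheduled, and with data collection still under way (341 participants had completed baseline measures by May 14, 2026), the contrast can be fixed before outcomes are analysed.
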